### Prescreening/screening

All patients who meet the clinical eligibility criteria identified at each MDT meeting will be recorded on the study screening log by the researcher or research nurse. Screening will take place at the outpatient clinic consultation when treatment options are discussed by the surgeon/oncologist. The researcher/clinician will attend the consultations for eligible patients. If appropriate at this stage, the purpose of the study will be explained and patients will be given the patient information leaflet to take away. Most patients will be booked for repeat visits to the head and neck clinic prior to finalising their treatment plan. Due consideration will be given to ensuring that the study information is discussed at an appropriate time after the diagnosis. Patients will be given a minimum of 24 hours after receiving the patient information sheet before a mutually agreed time is arranged to answer any further questions to assist patients in deciding about whether to participate. The time frame was chosen because most patients return to the hospital for other tests the day after their clinic visit. This offers an opportunity to answer questions in person and obtain signed consent if appropriate. Patients will be reassured that participation is voluntary with the freedom to withdraw at any stage, and that participation in the study will not affect or delay their main treatment.

### Enrolment/consent

Informed consent will be obtained by the researcher/clinician (RG) or a trained research nurse. Following informed consent and generation of a patient study identification number, the patient will be entered onto the study enrolment log and randomised to either the SIP SMART intervention or usual care group as detailed below.

### Randomisation and allocation

Eligible patients will be randomly assigned in a 1:1 ratio between usual care and intervention groups (figure 3 for trial flow chart). Patients will be stratified by first-line treatment; surgery or chemoradiation, a known factor that impacts swallowing outcomes.^13^ It will therefore be necessary to ensure a balance of primary treatment modality across the groups. Owing to the small numbers in this study, random block permutations will be employed to ensure a close match in numbers in the intervention and usual care groups at any given point during the trial.

**Figure 3 BMJOPEN2016014167F3:**
[figure not shown]
Trial flow chart.

Patients will be allocated to one of two groups using an online computer-generated randomisation service provided by an external company: http://www.sealedenvelope.com/. The company is registered with the Information Commissioners Office (ICO) and inspected by the MHRA (UK trials regulator). Following consent, the researcher or research nurse will enter the password-protected website and complete relevant information regarding first-line treatment. Randomisation is immediate, and the group allocation is emailed within a few minutes. This process is undertaken in the presence of the patient after signed consent is obtained, ensuring that the allocation is concealed until this point and simultaneously made known to the patient and researcher. Allocation is not blinded as the patient and staff will be aware that the new intervention includes a baseline videofluoroscopy or X-ray of swallowing. Patients allocated to the usual care group are advised that they will be sent an appointment in the post to see an SLT prior to their treatment as per the usual care pathway. Patients allocated to the intervention group are given an appointment and a further information leaflet on having a videofluoroscopy to assess how well the muscles and nerves function when swallowing different textures of food and drink. All patients are given three questionnaires to complete and return prior to their appointment with the SLT.

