### Baseline and follow-up outcome measures

Swallowing is a multidimensional phenomenon that may be measured by a number of different indicators including: patient-reported outcome measures, clinician ratings and scores from instrumental assessments such as videofluoroscopy and fibre-optic endoscopic evaluation of swallowing. This range of outcomes can prove problematic when synthesising findings from multiple studies. In this feasibility trial, we have selected a similar panel of swallowing outcome measures to that used in concurrent UK trials for HNC (radiation and surgery-based trials using a swallowing outcome measure),^43^ as well as measures collected as part of routine clinical practice (table 1). Outcome measures will be collected at baseline and 1, 3 and 6 months after treatment. Six months represents a relatively stable time point in the recovery trajectory for patients with HNC and was therefore selected as an appropriate end point.^21^
^36^ Patient weight, body mass index and use of feeding tube will also be recorded at all time intervals. The MD Anderson Dysphagia Inventory (MDADI)^44^ will be used to determine swallowing related QOL. We have chosen to collect information on health-related QOL via the Functional Assessment of Cancer Therapy and Head and Neck subscale (FACT-HN) as this questionnaire was identified as the most preferred by patients with HNC when compared with other QOL questionnaires.^45^

**Table 1 BMJOPEN2016014167TB1:** Outcome measures and time points

Measure	T0 baseline	T1 1 month	T2 3 months	T3 6 months
Background information	X			
Measures taken as part of usual care				
Performance Status Scale (PSS)	X	X	X	X
Maximal incisor opening (mouth opening)	X	X	X	X
Functional Intraoral Glasgow Scale	X	X	X	X
100 mL Water swallow test	X	X	X	X
Additional measures for trial				
MD Anderson Dysphagia Inventory	X	X	X	X
General Self-Efficacy Scale	X			X
Self-reported adherence question		X	X	X
HRQOL—FACT–HN	X	X	X	X
Modified Barium Swallow Impairment Score and Penetration/Aspiration score				X
Acceptability to participation/randomisation questionnaire				X

HRQOL—FACT–HN, Health Related Quality of Life- Functional Assessment of Cancer Treatment- Head & Neck subscale.

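### The three baseline questionnaires are handed out after the patient has been told the allocation, so the patient-reported T0 scores are pre-intervention but not pre-randomisation

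*Protocol article*

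**What the plan says.** The article sets out the order of events in two places. Under Enrolment/consent, once consent is given and a study number generated, "the patient will be entered onto the study enrolment log and randomised to either the SIP SMART intervention or usual care group". No baseline assessment is placed between consent and randomisation.

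Under Randomisation and allocation (the text following Figure 3), the sequence is:

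- "Randomisation is immediate, and the group allocation is emailed within a few minutes". This is done with the patient present, and the result is "simultaneously made known to the patient and researcher".
- There is no blinding: "Allocation is not blinded as the patient and staff will be aware that the new intervention includes a baseline videofluoroscopy".
- The arms then receive different information. "Patients allocated to the intervention group are given an appointment and a further information leaflet on having a videofluoroscopy", whereas usual-care patients are told that an appointment will come by post.
- The paragraph ends: "All patients are given three questionnaires to complete and return prior to their appointment with the SLT".

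The three forms are not named there. Table 1 marks three patient-completed scales at T0: the "MD Anderson Dysphagia Inventory", the "General Self-Efficacy Scale" and the FACT-HN. The MDADI and FACT-HN are repeated at 1, 3 and 6 months, and self-efficacy at 6 months only.

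**The concern.** A baseline score is normally taken before allocation so that any difference between arms is due to chance alone. Here the patient answers knowing the arm and having received different materials and appointment arrangements. Self-efficacy is the scale most plausibly affected by learning whether one will receive a behavioural package, but answers on swallowing-related and general quality of life could move too. Willingness to send the forms back could also depend on the arm.

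Three stated purposes of the study are touched:

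- Completeness of data collection is one of its aims, and baseline return could depend on allocation.
- The Analysis section says that effect-size estimates will inform the sample size of the definitive trial. Any such estimate that uses baseline would carry the shift.
- The study exists to test research procedures, so an order left unchanged here may be carried into the larger trial, where it would matter more.

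**Working it through.** **The plan's own figure.** About 70 referrals a year × 0.60 recruited × 9/12 of a year = 31.5, which agrees with the stated 32 patients. At 1:1 allocation that is 16 per arm. The point does not depend on this figure; it sets the scale for what follows.

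**Order of events.** Enrolment/consent goes straight from consent to randomisation. Randomisation and allocation goes from disclosure to arm-specific information to questionnaires. The return deadline is tied to the SLT appointment, which is arranged after allocation. No section places a patient-reported measure before allocation. The count of three forms equals the number of patient-completed scales at T0 in Table 1.

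**Effect on a between-arm comparison.** Let b be the between-arm shift in the baseline score caused by knowing the arm, in SD units, with the follow-up score unaffected. Let rho be the within-arm correlation between baseline and follow-up, with equal SDs at both times. The document gives neither b nor rho, so both are assumptions.

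- Change-score comparison: bias = −b. For b = 0.2 this is −0.2 SD.
- Baseline-adjusted comparison: bias ≈ −rho × b. For b = 0.2: 0.3 × 0.2 = 0.06, 0.5 × 0.2 = 0.10 and 0.7 × 0.2 = 0.14, so −0.06 to −0.14 SD.
- Comparison of 6-month scores alone: no bias from this source.

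**Could the trial's data reveal the shift?** With 16 per arm, equal SDs and no missing forms:

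- Standard error of the baseline difference = √(2/16) = 0.35 SD, so chance alone gives a 95% range of ±1.96 × 0.354 = ±0.69 SD.
- Power to detect b (two-sided 5%, normal approximation) ≈ Φ(b/0.354 − 1.96). For b = 0.2: Φ(0.57 − 1.96) = 8%. For b = 0.5: Φ(1.41 − 1.96) = 29%.

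A shift of either size would probably go unnoticed, so a comparison of the arms at baseline cannot serve as reassurance.

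**The case against.** The strongest reply is that these are still pre-intervention baselines. Both arms must return the forms before seeing the therapist, so neither the exercises, the videofluoroscopy nor the behaviour-change content can have influenced them. That is correct, and it limits the exposure to knowledge of the arm plus an appointment and a leaflet.

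The setting also reduces the weight. The analysis is mainly descriptive, no primary efficacy test is planned, and the article specifies neither a change-score nor a baseline-adjusted analysis. None of the four success criteria requires a comparison of baseline patient-reported scores between arms. The target difference for the definitive trial is to come from the literature. All of this stands and bears on importance, but it does not alter the order of events. No later analysis plan can turn a post-allocation score into a pre-randomisation one.

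Two facts are inferred. The three forms are identified by matching the count in Table 1, and Figure 3, the flow chart, is not available here and might make the order clearer.

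A reader might be tempted to go further in four ways that the document does not support:

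- *That allocation concealment fails.* It does not: the allocation is unknown until after consent.
- *That the SDs and the baseline-to-follow-up correlation passed to the definitive trial are spoiled.* A uniform shift by arm leaves the within-arm SDs, the within-arm correlation and the residual SD from a model with an arm term unchanged. Only the between-arm contrast moves.
- *That the bias is a known share of the treatment effect.* The article states no target difference, so no such share can be given.
- *That usual-care patients will be disappointed and withhold their forms, or that one clinician records every clinician-rated T0 measure in the intervention arm.* Nothing shows the first. For the second, the article says who delivers the intervention, not who records T0.

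**Conclusion.** The point holds as a weakness in the order of procedures. As written, the patient-reported T0 scores are taken after disclosure of the allocation, and both the answers and the return of forms could depend on the arm. Whether they would is not shown.

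Under the assumed shift of 0.2 SD, the bias is 0.2 SD for a change-score comparison and 0.06 to 0.14 SD for a baseline-adjusted one. It is nil where baseline is not used. These figures illustrate the mechanism and are not estimates for this trial. The weight is moderate to low in this feasibility study. The point is worth acting on because the remedy is cheap and the procedure may be reused in the definitive trial.

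**What to change.** Set the order as signed consent, then completion of the three questionnaires, then opening of the randomisation website. Name the three forms in the text and make their completion an entry check before randomisation.

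If a patient cannot complete them at that visit, mark those scores as post-allocation and pre-intervention, and report return rates by arm.

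The clinician-rated T0 measures (such as the water swallow test, Performance Status Scale and mouth opening) belong to the SLT consultation described under Interventions and procedures. Moving them ahead of allocation would mean rearranging that consultation. They may stay where they are, labelled as post-allocation and unblinded.

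The cost is a somewhat longer consent visit. The Discussion stresses how hard it is to approach patients soon after a cancer diagnosis, and recruitment rate is a success criterion. The added time should therefore be recorded with the recruitment and consent times that the study already plans to report. No sample-size figure changes.

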### Interventions and procedures

*Usual care group*: This group will receive the usual pretreatment care offered by the SLT prior to their upcoming surgery and/or chemoradiation. The SLT clinical team consisting of four members participated in a series of consensus meetings regarding the delivery of usual care to facilitate equipoise. All four team members involved in the delivery of usual care have also undergone good clinical practice (GCP) training. A usual care manual was written and agreed by the SLT clinical team prior to initiation of the study to ensure a level of consistency among the clinicians. Usual care pretreatment is one 45 min consultation as described below:
General case history taking and introduction of SLT role.Clinical baseline screening of swallowing and communication function. This is usually based on an oro-motor assessment; 100 mL water swallow test;^40^ a clinician-rated Performance Status Scale indicating the normalcy of diet texture and public eating score;^41^ and a clinician-rated scale for chewing, communication and swallowing.^42^ Maximal jaw opening using a TheraBite measure and voice quality ratings using the GRBAS (Grade of Hoarseness, Roughness, Breathiness, Asthenia, Strain) rating scale are also recorded.The patient is provided with a general overview of the planned treatment (surgery or chemoradiation) and information about the likely side effects such as mucositis and taste changes and impact of treatment on swallowing and communication function.General advice and exercises are offered to patients planned for chemoradiation at this appointment. Patients are provided with a general exercise sheet that includes instructions for eight different swallowing exercises, for example, passive jaw stretches. This is included as part of the information pack given to all patients receiving radiotherapy. Patients are advised that it *may* be helpful to start doing the exercises before treatment.

*Intervention group*: Patients in the intervention group will be pretreated according to the SIP SMART protocol that includes the specific components of the new intervention in addition to all aspects of usual care. The intervention takes place over two 45 min consultations that may follow each other on the same day or with a day or two between them depending on patient preference. The new intervention will be delivered by one clinician (RG) who completed a 5-day intensive training course in behaviour change (UCL Centre for Behaviour Change), supplemented by online training in coding BCTs, as well as ongoing mentorship from an expert in behaviour change. Specific details of the new intervention have not been explicitly shared with clinicians delivering usual care to minimise contamination. Broad differences include the following:
Patients will undergo a radiological assessment of their swallow function in the fluoroscopy suite at the hospital site. This procedure is part of the SIP SMART intervention informing the selection of targeted exercises, and is used as part of patient education. A standard protocol for this clinical procedure will be adopted for the study.^35^ The patient will be asked to swallow a variety of food textures; fluoroscopic images of the lateral and anterior–posterior plane captured at a rate of 30 frames per second will be recorded on a swallow workstation (Digital Kay Pentax Swallow workstation, USA). This will be available for later analysis of swallow physiology. The fluoroscopy screening time is usually 2–3 min.Patients will subsequently be shown a video animation (Dysphagia App, Northern Speech Services, USA) to explain the basic mechanics of swallowing and to orientate them to key structures such as the tongue, base of tongue, airway and oesophagus. Patients will thereafter be shown their own videofluoroscopy and helped to identify the key structures using this newly acquired knowledge. The clinician will encourage the patient to provide commentary and or ask questions as they watch their own swallowing.The videofluoroscopy assessment will be used to tailor the information, advice and exercises given to the patient during the pretreatment session and to facilitate discussion about the rationale for exercises and possible consequences of not doing exercises.Further detail about the intervention content and behavioural strategies used is provided in the SIP SMART manual. This is not included in this paper, but can be requested from the first author.

Patients in both groups will follow the usual care pathway for SLT rehabilitation post treatment (see figure 3 for trial flow chart). The number of SLT rehabilitation sessions for all patients will be recorded. Patients will be informed that exercises may be amended post treatment based on updated swallowing assessment.

### Baseline and follow-up outcome measures

Swallowing is a multidimensional phenomenon that may be measured by a number of different indicators including: patient-reported outcome measures, clinician ratings and scores from instrumental assessments such as videofluoroscopy and fibre-optic endoscopic evaluation of swallowing. This range of outcomes can prove problematic when synthesising findings from multiple studies. In this feasibility trial, we have selected a similar panel of swallowing outcome measures to that used in concurrent UK trials for HNC (radiation and surgery-based trials using a swallowing outcome measure),^43^ as well as measures collected as part of routine clinical practice (table 1). Outcome measures will be collected at baseline and 1, 3 and 6 months after treatment. Six months represents a relatively stable time point in the recovery trajectory for patients with HNC and was therefore selected as an appropriate end point.^21^
^36^ Patient weight, body mass index and use of feeding tube will also be recorded at all time intervals. The MD Anderson Dysphagia Inventory (MDADI)^44^ will be used to determine swallowing related QOL. We have chosen to collect information on health-related QOL via the Functional Assessment of Cancer Therapy and Head and Neck subscale (FACT-HN) as this questionnaire was identified as the most preferred by patients with HNC when compared with other QOL questionnaires.^45^

**Table 1 BMJOPEN2016014167TB1:** Outcome measures and time points

Measure	T0 baseline	T1 1 month	T2 3 months	T3 6 months
Background information	X			
Measures taken as part of usual care				
Performance Status Scale (PSS)	X	X	X	X
Maximal incisor opening (mouth opening)	X	X	X	X
Functional Intraoral Glasgow Scale	X	X	X	X
100 mL Water swallow test	X	X	X	X
Additional measures for trial				
MD Anderson Dysphagia Inventory	X	X	X	X
General Self-Efficacy Scale	X			X
Self-reported adherence question		X	X	X
HRQOL—FACT–HN	X	X	X	X
Modified Barium Swallow Impairment Score and Penetration/Aspiration score				X
Acceptability to participation/randomisation questionnaire				X

HRQOL—FACT–HN, Health Related Quality of Life- Functional Assessment of Cancer Treatment- Head & Neck subscale.

At 6 months, a videofluoroscopy will be conducted on all patients using the standardised Modified Barium Swallow Impairment Profile Protocol (MBS Imp Profile), and analysis.^35^ Three SLT clinicians who have completed a 25 hour online training module and obtained the minimum 80% reliability score will provide consensus ratings for these assessments. Standard assessment rating forms developed as part of the MBS Imp Profile will be used to score the videofluoroscopies. We will also rate aspiration from the videofluoroscopies, based on the widely used 8-point Penetration-Aspiration Scale (PAS).^46^

As we anticipate that adherence to swallowing exercises should be associated with better swallowing, we will also collect intermediate outcomes on adherence using two simple questions developed for this trial. The questions will ask about percentage adherence over a specified time, and a free text question to gather further information about any specific reasons for adherence/non-adherence to exercises.

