**Figure 2 BMJOPEN2016014167F2:**
[figure not shown]
Key stages of the *MRC complex interventions framework that informed the development and preliminary testing of the SIP SMART intervention. *Source: Craig *et al*, BMJ;2008. MRC, Medical Research Council; SIP SMART, Swallowing Intervention Package: Self-Monitoring, Assessment, Rehabilitation Training.

Although another complementary non-randomised UK trial of pretreatment swallowing intervention is planned,^37^ our SIP SMART trial is unique as it is based on an optimised pretreatment intervention using tailored exercises selected after physiological assessment of swallowing, and is directly informed by theoretically derived BCTs. Furthermore, comprehensive evaluation of a new SIP is likely best performed using a randomised controlled trial (RCT) design. Given the uniqueness of our SIP and proposed future RCT evaluation, a feasibility study was deemed imperative to ascertain viability within a NHS context, and to identify and address potential barriers to future roll out on a larger scale.

In particular, the aims of this feasibility study are as follows:
Assess the rate of recruitment of eligible participants and identify any specific barriers to recruitment.Determine the acceptability of randomisation, and the randomisation procedure to patients and the clinical care team.Determine retention and attrition over the time course of the study.Evaluate the ease of protocol implementation, including research processes, and identify barriers in the clinical setting.Evaluate a range of potential outcome measures, including the ease and completeness of data collection across various time points.Determine concordance between potential outcome measures and define the most suitable primary outcome for the definitive study.Collect data to inform future sample size calculation.

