### Analysis

We will use mainly descriptive analysis and summary statistics to address our aims. Study screening and enrolment logs will be used in determining the rate of recruitment into the study. All qualitative information (researcher diary), minutes of study-related discussions and meetings will be imported into NVIVO 10, a software database to facilitate the organisation and thematic coding of qualitative or textual data. The researcher is in a unique position of being embedded within the clinical team, and therefore able to make observations over the duration of the study in a naturalistic manner. This approach to process analysis arguably may provide more useful information than the use of post hoc focus groups and interviews that rely on participant memory and may be removed from context.^48^ Observing and collecting information in this way also means that the researcher can observe the interplay of other factors (eg, multiple studies competing for the same patient group, prevailing views of the treating consultant about the value of the proposed intervention and how busy the clinic is) that may reveal vital information about the barriers and facilitators to recruitment.

We will also report on the practicality of implementing the protocol, for example, obtaining timeslots for videofluoroscopy; average time taken for the recruitment and consent process; utility of the chosen randomisation method and suitability of the study-specific forms including the CRF. This information will be used to optimise components of the protocol and study process in preparation for a larger trial.

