As a range of outcome measures will be collected, we will look at the suitability of each measure, the ease of collection and the quality and completeness of the data collection. We will observe the relationships (concordance and discordance) between the different outcome measures to help inform the most suitable choice of primary and secondary measures for a definitive trial. Important parameters such as SD and estimates of effect size will be used to inform the sample size calculation. Based on the available literature, we will aim to specify the target difference (clinically meaningful difference) for the chosen primary outcome. The primary outcome measure will be chosen from potential candidate measures on the basis that it is valid, practical and feasible to obtain and has expert agreement (RCSLT clinical expert group) that it reflects a good summary measure to answer the question of whether the new intervention is effective in improving swallowing.

Patient acceptability to participation and randomisation will be determined using a previously developed questionnaire.^49^ Self-reported adherence to the intervention will be explored via a brief study questionnaire. Previous studies reported that full adherence to exercises during radiotherapy was under 15%.^27^
^30^ In a Danish study of a similar intervention to the current study, an average of 35% of patients reported doing their exercises at least once a day between 1 month and 11 months after treatment.^22^ We have therefore selected 35% as the minimum target adherence for our study.

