### Criteria for success

This study will be viewed as feasible to proceed to a definitive trial if:
a suitable outcome measure is determined, and sample size estimated;recruitment rate into the trial reaches an average of four patients a month;patients report generally positive views about participation and acceptance to randomisation as determined by questionnaire evaluation;patients in the intervention group are more adherent than those in usual care, with at least 35% of intervention group patients reporting satisfactory to good adherence to exercises.

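### The acceptability questionnaire behind a proceed condition is scheduled only at six months after treatment, so its result may be selectively favourable

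*Protocol article*

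**What the plan says.** The protocol article fixes the timing, the instrument and the use of the result.

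- **Timing.** In Table 1 (Baseline and follow-up outcome measures), the row "Acceptability to participation/randomisation questionnaire" has a single mark, under T3. The follow-up clock runs from cancer treatment.
- **Instrument.** The Analysis section states: "Patient acceptability to participation and randomisation will be determined using a previously developed questionnaire". No other patient-completed measure of acceptability is named.
- **Use.** The Criteria for success begin "This study will be viewed as feasible to proceed to a definitive trial if" and include that "patients report generally positive views about participation and acceptance to randomisation as determined by questionnaire evaluation". No numerical threshold or denominator is attached.
- **Aims.** The aims at the end of the Introduction include "Determine the acceptability of randomisation, and the randomisation procedure to patients and the clinical care team" and, separately, "Determine retention and attrition over the time course of the study".
- **Withdrawal.** Under Prescreening/screening, patients are told that "participation is voluntary with the freedom to withdraw at any stage".
- **Allocation.** Under Randomisation and allocation, the patient learns the allocation straight after consent, before cancer treatment starts.

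**The concern.** The patients who could say most about whether randomisation was acceptable include any who left because of their allocation. With one administration at the last visit, and none described at withdrawal or earlier, those patients are not scheduled to answer. The respondents are those who accepted randomisation and stayed. They are asked about an event more than six months in the past, with a course of cancer treatment in between.

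Nothing else in the Criteria for success makes up for this. The recruitment condition counts patients entering the study, not patients staying in it, and there is no retention condition. The trial could therefore lose patients over allocation and still meet both the recruitment and the acceptability conditions. The decision to proceed would then rest on views from a subset whose relation to the whole randomised group is unknown.

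**Working it through.** **Denominator.** Study population, setting and recruitment plan gives about 70 eligible patients a year, 60% uptake and about 9 months of recruitment: 70 × 0.60 × 9/12 = 31.5, which agrees with the stated 32. I use 32 as the number randomised.

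**What is not given.** The article states no expected attrition, no expected share of positive answers and no threshold. Everything below is illustration under assumed values.

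**Mixture.** Let k be the number lost before T3, p_c the share positive among those remaining and p_w the share positive among those lost.

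- Share among all randomised = [(32 − k) × p_c + k × p_w] / 32
- Overstatement by the T3 figure = (k/32) × (p_c − p_w)

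With p_c = 0.80:

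| Assumed attrition | k | Share of all 32 if p_w = 0.20 | Share of all 32 if p_w = 0.40 | Overstatement (points) |
|---|---|---|---|---|
| 10% | 3 | (23.2 + 0.6)/32 = 74.4% | (23.2 + 1.2)/32 = 76.3% | 3.7 to 5.6 |
| 20% | 6 | (20.8 + 1.2)/32 = 68.8% | (20.8 + 2.4)/32 = 72.5% | 7.5 to 11.3 |
| 30% | 10 | (17.6 + 2.0)/32 = 61.3% | (17.6 + 4.0)/32 = 67.5% | 12.5 to 18.8 |
| 40% | 13 | (15.2 + 2.6)/32 = 55.6% | (15.2 + 5.2)/32 = 63.8% | 16.2 to 24.4 |

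If p_w = 0.80, the overstatement is zero in every row. If p_w were above p_c, the T3 figure would understate the share.

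**Bounds without any assumption about those lost.** Take whole numbers of completers with about 80% positive, and count those lost first as all negative and then as all positive:

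| k | Positive among completers | Lower bound of 32 | Upper bound of 32 |
|---|---|---|---|
| 3 | 23/29 = 79% | 23/32 = 72% | 26/32 = 81% |
| 6 | 21/26 = 81% | 21/32 = 66% | 27/32 = 84% |
| 10 | 18/22 = 82% | 18/32 = 56% | 28/32 = 88% |
| 13 | 15/19 = 79% | 15/32 = 47% | 28/32 = 88% |

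The completers' figure stays near 80% throughout, while the range compatible with it widens from 9 to 41 points (3/32 to 13/32). A T3-only schedule gives no data to say where in that range the truth lies.

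**The case against.** There is a fair case for T3. The form asks about participation as well as randomisation, and participation, including the six-month videofluoroscopy, can be judged in full only at the end. Newly diagnosed patients already receive three questionnaires before the pretreatment appointment. Splitting an existing instrument so that its randomisation items come earlier assumes that the items are separable, which the article does not show. These arguments stand. They support keeping T3 and not splitting the form, but they do not argue against also offering the whole form at withdrawal.

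Other parts of the plan bear on acceptability. The screening and enrolment logs give the recruitment rate, the researcher diary and minutes record barriers, and attrition is to be reported, so a reader will see how many patients are missing from the questionnaire results. This also stands, but the acceptability condition is tied to the questionnaire and does not draw on those sources.

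The exclusion of withdrawn patients is inferred from the schedule. The article never says that they may not be asked, and a fuller protocol could provide an exit form. The point is therefore about what the printed schedule delivers if followed.

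Losses may also have nothing to do with randomisation. In stage III and IV cancer, patients may be lost through death or illness, and those losses need not make the result look better.

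Two stronger readings are tempting, and the article supports neither:

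- A reader might infer that the plan contradicts itself, because the Analysis section compares its approach favourably with "post hoc focus groups and interviews that rely on participant memory and may be removed from context". That sentence concerns process analysis by an embedded researcher, is hedged, and does not mention structured questionnaires. There is no contradiction.
- A reader might infer that the measure could never reveal that randomisation was unacceptable, or that the criterion is bound to be met. Dissatisfied patients can stay in follow-up and answer negatively, so that goes too far.

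**Conclusion.** The point holds as one of possible selection in a proceed condition. The timing, the instrument and the status of the result are all fixed in the article, and no earlier or exit administration is described. Followed as written, the condition is judged on those still in follow-up, more than six months after allocation, with no retention condition beside it.

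The size is unknown. The illustrated overstatement of about 4 to 24 percentage points rests on three assumptions: attrition of 10% to 40%, 80% of completers positive, and 20% to 40% of those lost positive. It is zero if those lost share completers' views, and its direction is plausible but not established. Because the condition has no threshold, the figures do not show that the decision to proceed would change. They show that the planned data cannot tell a harmless loss from an informative one. The change is worth making because it is cheap and the result feeds a go/no-go decision.

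**What to change.** 1. Keep the questionnaire at T3.
2. Offer the same questionnaire, unsplit, at withdrawal to patients who agree. Optionally give it at T1 as well, which is already a data collection point.
3. In the Criteria for success, judge acceptability against all randomised patients, by arm. Show the numbers who did not respond and the reasons for withdrawal where given, next to the decline rate from the screening log.
4. Where responses are missing, report the bounds shown above alongside the observed share.

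The cost is one short extra form for some patients and an amendment to one row of Table 1, with matching wording in the criterion. Some withdrawing patients will decline the form, so selection is reduced, not removed. That is why non-response needs to be displayed.
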